##### Cardiometabolic Outcomes

Fasting (12-hour fast) blood is drawn from the antecubital vein (~30 cc) by a trained phlebotomist. For each sample, a total of six 10 mL tubes will be collected, three ethylenediaminetetraacetic acid and three Serum tubes, along with one additional lavender-topped tube (whole blood in ethylenediaminetetraacetic acid), for a total of 62 mL of blood drawn at each testing timepoint. Samples are centrifuged and then aliquoted and stored at –80 °C for future measures. Blood samples will be transported to Brigham Research Assay Core near the study end for batch-testing analysis of glucose, high-density lipoprotein-cholesterol, low-density lipoprotein-cholesterol, insulin, insulin resistance (Homeostatic Model Assessment for Insulin Resistance), triglycerides, and glycosylated hemoglobin. Future measures will include the analysis of additional biomarkers.

Lean mass, fat mass, and body fat % are obtained from the whole-body DEXA scan (completed only at baseline and postintervention testing timepoints). Premenopausal participants complete a pregnancy test (urine sample) prior to the body composition assessment to ensure the participant is not pregnant. BMI in kg/m^2^ will be calculated from height and weight. A constant tension tape measure is used to obtain waist circumference defined as the distance around the waist using the umbilicus as the reference point. A constant tension tape measure is used to obtain hip circumference defined as the distance around the widest girth of the buttocks using the greater trochanter as a landmark. Body composition is assessed via bioelectrical impedance using a validated device (Tanita 780, Arlington Heights, Illinois). The device will estimate body fat using an algorithm based on age, sex, height, and body weight.

#### Tertiary Outcomes—Posttransplant Clinical Outcomes

Posttransplant clinical outcomes are assessed through a review of patient medical records and include the Hematopoietic Cell Transplantation-Comorbidity Index, length of hospital stay, readmission rates, and treatment-related adverse events.

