### Randomization and Blinding

Participants are randomly assigned to either the exercise group or the waitlist control group in a 1:1 ratio following the completion of baseline assessments. Prior to the trial start, the study biostatistician prepared the randomization schema and provided the randomization allocation to staff through a web-based application (REDCap [Research Electronic Data Capture]; Vanderbilt University) [24] to blind study investigators to the randomization process. The nature of the exercise intervention prevents blinding the study participants, interventionists, and outcome assessors. However, study investigators adhere to a set protocol to standardize outcome assessments and avoid bias.

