### Outcome Measures

#### Overview

The outcomes are assessed at baseline, postintervention, and 30-day posttransplant follow-up. All measures are performed by trained study personnel at the Dana-Farber Cancer Institute. Postintervention assessment (week 10; visit 27) includes a reassessment of baseline measures. The 30-day post-ASCT follow-up (week 14-15; visit 28) consists of a reassessment of baseline measures (not including dual-energy x-ray absorptiometry [DEXA]) in addition to Hematopoietic Cell Transplantation-Comorbidity Index, length of hospital stay, readmission rates, and treatment-related adverse events. If the intervention is selected following the ASCT recovery period, the waitlist control group testing (visits 29-54) includes assessment of baseline measures (not including DEXA) pre- and postintervention (visits 29 and 54, respectively).

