### Adverse Events

Participants are evaluated for potential adverse events (eg, pain, muscle soreness, nausea, and bone pain) during each exercise session in the study period. Phone numbers for study staff are provided to report potential intervention-related adverse events. The National Cancer Institute Common Terminology Criteria for Adverse Events V5 is used to assess participants and documented by the study staff at each exercise session. Study progress and injuries are reported upon during weekly meetings through in-person updates, phone calls, or weekly email updates. Adverse events, both serious and nonserious, and deaths encountered from initiation of study intervention, throughout the study, and within 30 days of the last study intervention sessions, are followed to resolution, or until the principal investigator determines the participant as stable or the event as irreversible, or the participant is lost to follow-up.

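### The posttransplant adverse-event outcome is limited to treatment-related events in an unblinded trial, so a causality judgement enters a comparison that randomization would otherwise protect

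*Protocol article*

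**What the plan says.** The section Tertiary Outcomes—Posttransplant Clinical Outcomes names these items: "Hematopoietic Cell Transplantation-Comorbidity Index, length of hospital stay, readmission rates, and treatment-related adverse events". The same restricted wording appears in Objectives and in the Outcome Measures overview, so it is not a slip of the pen. On the source of the data it says: "Posttransplant clinical outcomes are assessed through a review of patient medical records".

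On blinding, the Randomization and Blinding section says: "The nature of the exercise intervention prevents blinding the study participants, interventionists, and outcome assessors". The mitigation it offers is that "study investigators adhere to a set protocol to standardize outcome assessments and avoid bias". The Outcome Measures overview adds that "All measures are performed by trained study personnel at the Dana-Farber Cancer Institute".

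Statistical Analysis treats each clinical outcome as an exploratory assessment of group differences, with two-sample t tests for continuous variables and Fisher's exact test for categorical ones. Its examples are length of stay, number of comorbidities and readmission; adverse events are not among them.

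The Adverse Events section describes a separate collection with no causality filter: "Adverse events, both serious and nonserious, and deaths encountered from initiation of study intervention, throughout the study, and within 30 days of the last study". The 30 days there run from the final exercise session. In the same section, "The National Cancer Institute Common Terminology Criteria for Adverse Events V5 is used to assess participants", with documentation at each exercise session.

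**The concern.** Randomization already supplies the causal contrast: if prehabilitation changes toxicity after transplant, the two arms will differ in all events. Sorting events by presumed cause after randomization puts a human judgement between the event and the outcome, and in this trial no blinding of that judgement is described. Someone who knows that a patient trained for eight weeks may be slower, or quicker, to ascribe a given event to the transplant. Attribution can then differ between arms when the events do not, or cancel a difference that is real.

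The article's Conclusions say the results should inform larger trials. What carries forward from a trial of 30 patients is mainly the estimate, so a biased tolerance estimate matters even if no test is significant.

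**Working it through.** **1. What treatment means.** The article usually calls the exercise program the intervention, and its Adverse Events section refers to intervention-related events when it means harm from exercise. It uses treatment for medical therapy: neoadjuvant treatments in the inclusion criteria, and treatment-related symptoms in the Discussion. The adverse-event item also sits in a list of posttransplant outcomes taken from medical records. The coherent reading is toxicity of transplant or myeloma therapy. Both arms are exposed to that, so the outcome is defined in both, and the filter contributes only the attribution step.

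**2. Whether the Adverse Events section supplies an unfiltered count.** Its active assessment is at exercise sessions, which waitlist controls do not have before the 30-day post-ASCT visit. Its window starts with the study intervention and ends 30 days after the last session. With eight weeks of sessions, 8 + 30/7 ≈ week 12.3, before the week 14-15 follow-up, unless the phrase about the whole study extends it. It is not described as a symmetric posttransplant count in both arms.

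**3. The plan's own figures.** None is given for this outcome. The only power statement concerns muscle strength: d = 1.15, 15 per group, 10% dropout, two-sided alpha .05. That reproduces. Noncentral-t power is 80.3% at 13 per arm and 81.9% at 13.5 per arm, and 1.15 × 16.8 kg = 19.32 kg against the stated 19.3 kg. Nothing in this point changes it.

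**4. How attribution acts.** Observed rate = true event rate × proportion attributed. All rates below are assumptions. Rejection is the exact probability that a two-sided Fisher test gives p ≤ .05 with 15 per arm.

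| True rate, control / exercise | Attributed, control / exercise | Observed, control / exercise | Rejection |
|---|---|---|---|
| 60% / 60% | 85% / 65% | 51% / 39% | 4.1% |
| 80% / 80% | 70% / 70% | 56% / 56% | 1.6% |
| 80% / 80% | 90% / 70% | 72% / 56% | 6.6% |
| 80% / 80% | 90% / 50% | 72% / 40% | 26.4% |
| 80% / 80% | 90% / 30% | 72% / 24% | 62.9% |
| 80% / 40% | 100% / 100% (all events counted) | 80% / 40% | 44.7% |
| 80% / 40% | 45% / 90% | 36% / 36% | 1.6% |

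The first five rows have no true effect. A 20-point attribution gap moves the estimate by 12 points (0.60 × 0.20) or 16 points (0.80 × 0.20) but seldom produces significance. Gaps of 40 to 60 points are needed for rejection of 26% to 63%. The last two rows show the opposite error: a true 40-point difference disappears.

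**5. A check on the remedy.** A yes/no outcome of any grade 3 or higher event could sit near its ceiling after transplant. With assumed rates of 95% and 85%, rejection at 15 per arm is 3.0%. A summary that keeps the grade or the number of events is safer than that dichotomy alone.

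**The case against.** Several objections carry weight.

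- **Condensation.** A journal article may leave to the full protocol the definition of treatment, the attribution rule and the name of the person who extracts the records. That stands, and none of these omissions is the point here. The filter itself is stated, and defining it more closely would not remove it.
- **Who judges relatedness.** The article names no extractor. Relatedness may already be written in the notes of treating clinicians, and the article does not say whether they know the arm. Unblinded attribution is therefore an inference from the general statements on outcome assessors and study personnel. It is a fair one, since no blinded attribution is described, but it is an inference.
- **Other safety data.** Events and deaths are also collected without a causality filter, and length of stay and readmission need no attribution. So the restriction applies to one tertiary item and not to all safety data, and a misleading tolerance result could be checked against the other items.
- **Size.** The rates are assumed, and a 20-point gap seldom yields a significant test. That stands.

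A reader might also infer that treatment means the exercise program, so that controls could have no qualifying event and the arms could not be compared. The article's own vocabulary does not support that reading.

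**Conclusion.** The concern holds in limited form. The tertiary adverse-event outcome carries a causality filter that serves no purpose for a randomized comparison when both arms receive the treatment in question. With outcome assessors unblinded, the filter exposes the comparison to differential attribution in either direction. The documents do not show that such bias will occur, and its size cannot be derived from them. Under the assumed rates, the bias ranges from a shift in the estimate that tests rarely detect to the complete masking of a true difference.

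The conclusion rests on two readings: that treatment means transplant or myeloma therapy, and that the statement on unblinded assessors extends to attribution of posttransplant events. The practical impact is modest. The outcome is tertiary, its analysis is exploratory and unpowered, and the primary analysis and sample size are untouched.

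**What to change.** Redefine the tertiary item as CTCAE v5 adverse events of any cause from ASCT to day 30, abstracted from the same medical records over the same window in both arms. Summarise by grade, for example the maximum grade or the number of events per patient, and do not rely only on any grade 3 or higher event as yes or no. The two-sample Wilcoxon test, already listed in Statistical Analysis for other endpoints, would suit such summaries. Report relatedness descriptively, stating which treatment is meant and, where possible, having it judged without knowledge of the arm.

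The cost is a wording change and slightly more chart abstraction within a review already planned. Some events unrelated to prehabilitation will be included and will dilute the contrast; how much cannot be stated from the documents. With 3 participants randomized as of October 2024, the change affects little completed work.

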#### Exploratory Outcomes

The treatment trajectory for patients with multiple myeloma incorporates prehabilitation and rehabilitation, though when a patient experiences the most benefit is unclear, as they occur at different stages of the treatment trajectory. Therefore, a self-controlled single-group analysis will be done on the participants from the waitlist control who elect the exercise program post-ASCT to assess how an 8-week exercise intervention completed post-ASCT affects muscle strength, physical capacity, patient-reported outcomes, and cardiometabolic health outcomes.

### Adverse Events

Participants are evaluated for potential adverse events (eg, pain, muscle soreness, nausea, and bone pain) during each exercise session in the study period. Phone numbers for study staff are provided to report potential intervention-related adverse events. The National Cancer Institute Common Terminology Criteria for Adverse Events V5 is used to assess participants and documented by the study staff at each exercise session. Study progress and injuries are reported upon during weekly meetings through in-person updates, phone calls, or weekly email updates. Adverse events, both serious and nonserious, and deaths encountered from initiation of study intervention, throughout the study, and within 30 days of the last study intervention sessions, are followed to resolution, or until the principal investigator determines the participant as stable or the event as irreversible, or the participant is lost to follow-up.

### Sample Size

We anticipate recruiting 1-2 participants per month, based on the accrual rates (3 to 4 participants per month) of previous exercise intervention studies [48]. A total of 30 eligible participants will be entered into this study and randomly assigned to the intervention and the control groups in a 1:1 ratio (15 per group). The sample size is based on general recommendations (24 to 50) for pilot studies in general [49-51] and this study provides 80% power to detect the effect size of Cohen *d*=1.15 (taking account of 10% dropout) at .05 two-sided α level.

### Statistical Analysis

The primary analysis is a mean difference in percent change from baseline (week 0, preintervention), between the intervention and the control groups in lower leg muscle strength over 2 time points: pretransplant (week 9, postintervention), and posttransplant (week 14-15, 30-day post-ASCT follow-up). Linear mixed-effects models are used to compare the between-group differences at postintervention and follow-up after adjusting for baseline value of the outcome and covariates, where the intervention indicator and time are included as fixed effects and participants are included as random effects. From previous studies, the estimated standard deviation of change in muscle strength (measured through leg press) from baseline to pretransplant is 16.8 kg. Thus, this study will detect a between-group mean difference of 19.3 kg with 80% power. The primary analyses will be based on the intention-to-treat principle including all randomized participants. The same analyses will also be performed with the per-protocol population.

To test hypotheses related to differences in physical capacity, patient-reported outcomes, and cardiometabolic health outcomes across groups at study completion, standard statistical techniques are used to assess within-group differences among each end point (ie, 2-tailed *t* test or Wilcoxon signed rank test, proportions, and corresponding 95% exact CI, etc) and between-group differences (ie, 2-tailed *t* tests, two-sample Wilcoxon tests, generalized linear mixed-effects model for longitudinal measurements, and so on). As an exploratory analysis to assess group differences, each clinical outcome as continuous variables (ie, length of hospital stay and the number of comorbidities) and categorical variables (ie, hospital readmission) is analyzed using 2-sample *t* tests for continuous variables and Fisher exact test will be used for analyzing categorical variables. An exploratory analysis to assess differences in the postintervention self-elected exercise for the waitlist control group will be assessed for end points of aim 1-2 using paired *t* tests and Cohen d is calculated to determine the effect size.

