### Objectives

The goal of this randomized controlled trial, “Prehabilitation Exercise Training in Multiple Myeloma Patients Undergoing Autologous Stem Cell Transplantation: The PROTECT (Prehabilitation Exercise Training in Multiple Myeloma Patients Undergoing Autologous Stem Cell Transplantation) trial (Figure 1),” is to assess the impact of digitally supervised, individually tailored prehabilitative aerobic and resistance exercise in patients with multiple myeloma undergoing ASCT (Figure 1) on lower limb muscle strength (primary objective) in the exercise group compared to the waitlist control group. The secondary and tertiary objectives will examine physical capacity (physical function and cardiorespiratory fitness) and patient-reported outcomes (fatigue and quality of life), cardiometabolic health outcomes (biomarkers and body composition), along with posttransplant clinical outcomes including Hematopoietic Cell Transplantation-Comorbidity Index, length of hospital stay, readmission rates, and treatment-related adverse events. Finally, due to the nonprofound changes given the limited intervention period, the exploratory objective is to evaluate the exercise intervention completed post-ASCT on muscle strength, physical capacity, patient-reported outcomes, and cardiometabolic health outcomes. We hypothesize that prehabilitative aerobic and resistance exercise will improve lower limb muscle strength prior to receiving ASCT and 30 days posttransplant in the exercise group compared to the waitlist control group.

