#### Primary Outcomes—Lower Limb Muscle Strength

Percent change in lower limb muscle strength is the primary outcome. The 1RM value will be estimated from 10RM muscle strength tests on the leg press or leg extension. The test selected is dependent on the bone lesion site and the participant's health status. Additional strength testing using approximately 5 resistance band exercises individually selected for participants based on health status; 1RM values will be calculated and reported using validated equations [29,30]. Alternative strength exercises will be used to ensure participants’ safety as needed for both testing and training periods. Following a warm-up, 3-5 attempts will be given to reach the final 10RM load with a 2-minute rest period between attempts.

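### The terms listed for the primary mixed model give one group effect common to both visits, while the text promises visit-specific differences and the 80% power is for the pretransplant change alone

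*Protocol article*

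**What the plan says.** All of this is in the Protocol article.

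- **Outcome.** Primary Outcomes: "Percent change in lower limb muscle strength is the primary outcome".
- **Time points.** Statistical Analysis defines the primary analysis as the between-group mean difference in percent change "in lower leg muscle strength over 2 time points: pretransplant (week 9, postintervention), and posttransplant (week 14-15, 30-day post-ASCT follow-up"). The two visits are not ranked.
- **Purpose of the model.** Same section: "Linear mixed-effects models are used to compare the between-group differences at postintervention and follow-up", after adjustment for the baseline value and covariates.
- **Terms of the model.** The same sentence ends: "where the intervention indicator and time are included as fixed effects and participants are included as random effects". No intervention-by-time term is mentioned.
- **Hypothesis.** Objectives: the programme "will improve lower limb muscle strength prior to receiving ASCT and 30 days posttransplant in the exercise group compared to the waitlist control group".
- **Power.** Statistical Analysis: "the estimated standard deviation of change in muscle strength (measured through leg press) from baseline to pretransplant is 16.8 kg", from which it concludes that "this study will detect a between-group mean difference of 19.3 kg with 80% power". Sample Size gives the same claim as Cohen d = 1.15, with 15 per group, 10% dropout and a two-sided .05 level.

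**The concern.** A model with intervention and time as main effects has one intervention coefficient. It constrains the group difference to be the same before transplant and 30 days after it. It therefore cannot supply the two visit-specific differences that the first half of the same sentence promises, unless a term is added that the sentence does not list.

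The constraint matters here because the transplant lies between the two visits and the supervised programme ends before it. If a strength gain is present before transplant and partly lost by day 30, the common coefficient blends the two. The article nowhere states that it expects a constant effect.

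The power statement rests on a third quantity, a single comparison of change up to transplant. So the article contains three candidate primary quantities: the pretransplant difference, a pair of visit-specific differences, and an average over both visits. The text does not settle which one is tested. Left open, the choice could be made after the data are seen.

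**Working it through.** **Inputs from the article.** 15 per group; 10% dropout; two-sided alpha .05; d = 1.15; SD 16.8 kg (baseline to pretransplant); detectable difference 19.3 kg; power 80%.

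**Assumptions, not in the article.** Correlation ρ between the two visits of 0.3 to 0.7; the fraction f of the pretransplant effect that remains at day 30; complete data at both visits; equal SDs at both visits; no gain in precision from baseline or covariate adjustment.

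**Step 1: reproduce the stated power.** 1.15 × 16.8 = 19.32 kg, which matches 19.3 kg. Evaluable per arm: 15 × 0.9 = 13.5, rounded down to 13. For a two-sample t test at one visit, the noncentrality is 1.15 × √(13/2) = 2.93 on 24 degrees of freedom, with critical value 2.064. Power is 80.3%. The stated figure is correct for one comparison at one visit.

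**Step 2: what the listed terms estimate.** With complete data and equal SDs, the common group effect is the average of the two visit differences. In SD units:

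- effect = 1.15 × (1 + f)/2
- SD of a participant's two-visit average = √((1 + ρ)/2)
- noncentrality = effect ÷ SD × √(13/2)

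For example, with f = 0.5 and ρ = 0.5: effect 0.8625 (14.5 kg), SD 0.866, ratio 0.996, noncentrality 2.54, power 68%.

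| Effect left at day 30 | Quantity estimated | Power, ρ = 0.3 | ρ = 0.5 | ρ = 0.7 |
|---|---|---|---|---|
| all (f = 1) | 19.3 kg | 94% | 90% | 86% |
| half (f = 0.5) | 14.5 kg (75%) | 74% | 68% | 63% |
| none (f = 0) | 9.7 kg (50%) | 42% | 37% | 33% |

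**Step 3: where averaging starts to cost power.** Averaging and the single-visit test have equal power when (1 + f)/2 = √((1 + ρ)/2), that is, f = 2√((1 + ρ)/2) − 1. This gives f = 0.61, 0.73 and 0.84 for ρ = 0.3, 0.5 and 0.7. Above that fraction the averaged test has more power than 80%; below it, less.

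**Step 4: if the visits are tested separately at .05.** The pretransplant test keeps its 80.3%. If success at either visit counts, the chance of at least one false positive (bivariate normal, both nulls true) is 9.5%, 9.1% and 8.3% for ρ = 0.3, 0.5 and 0.7. If success at both visits is required, type I error does not exceed .05. A Bonferroni split at .025 each would lower power for d = 1.15 at one visit from 80% to 70% with 13 per arm.

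**The case against.** **The interaction may simply be unstated.** This is a condensed article. It says intervention and time are included, not that nothing else is, and the stated aim of comparing groups at each visit implies visit-specific contrasts. That is fair: a reader might infer that the trial has decided against an interaction, and the text does not show that. What stands is narrower. The article chose to list the model terms, and the terms listed do not produce the output named in the same sentence. That is a stated rule that does not match its stated purpose, not mere brevity.

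**An average over both visits is a coherent plan.** The definition over two time points can be read that way. It needs one coefficient and one test, and raises no multiplicity. Under a constant effect its power is 86–94%, so the 80% would be conservative. This reading still conflicts with the visit-specific wording and with a power statement built on the pretransplant change alone, so some correction is needed.

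**The 80% is not wrong on every reading.** A reader might infer that it describes no test the trial could run. It does describe the pretransplant test if the visits are tested separately at .05. The open issue on that reading is multiplicity. Even that arises only if a win at either visit counts; the hypothesis joins the two time points, which could mean that both are required.

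**The power losses are illustrative.** They depend on a retained fraction and a correlation that the article does not give. Missing data after transplant would move the common effect away from a simple average, and baseline adjustment could raise precision.

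**It is a pilot.** The sample size rests mainly on general recommendations for pilot studies, with power as an accompanying statement. This lowers the severity but does not remove the mismatch.

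**Conclusion.** The concern holds as a mismatch between three stated things: the comparison promised, the terms listed, and the quantity that was powered. The power arithmetic itself is sound (80.3% reproduced), and no change in sample size is called for.

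Its size depends on how much of the effect survives transplant. Under the assumptions listed in the working, power of the model as listed ranges from 86–94% (all remains) through 63–74% (half) to 33–42% (none). It is tempting to conclude that the trial is underpowered or that its type I error is inflated. The documents support neither as a fact: the first needs a substantial loss of effect by day 30, and the second needs separate unadjusted tests with success at either visit sufficient. The mismatch does not depend on these assumptions. It should be fixed, but it is not critical for a pilot of this kind.

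**What to change.** 1. Add the intervention-by-time term, with time as a factor, so that the model yields a difference at each visit.
2. Name the pretransplant (postintervention) contrast as the single primary test at two-sided .05. This matches the existing power calculation, and the stated 80% then stands with 30 participants.
3. Report the day-30 contrast from the same model as secondary, with a 95% CI.

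The cost is about one sentence of text, one or two model degrees of freedom, and secondary status for the day-30 half of the hypothesis. That last point is for the sponsor to accept or not.

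If an average over both visits is what the sponsor wants, the listed terms can stay. The text should then call the primary quantity an average, drop the promise of visit-specific primary comparisons, and restate the power for that average with its assumed correlation and day-30 effect. If both visits are to remain primary, the text should say whether both must succeed or either suffices, and, in the latter case, how alpha is divided. Only 3 participants had been randomized by October 2024, according to the Results section, and analysis had not started at that point.

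### Read in the ordinary way, the primary mixed model gives the pretransplant and posttransplant strength changes one shared variance, an unsupported assumption for visit-specific group comparisons that is cheap to remove

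*Protocol article*

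**What the plan says.** The Statistical Analysis section of the protocol article sets the primary analysis as a group difference in percent change in strength from baseline, over one visit before transplant and one about 30 days after it. On purpose it says: "Linear mixed-effects models are used to compare the between-group differences at postintervention and follow-up", with adjustment for the baseline value and covariates. On the model terms it says: "the intervention indicator and time are included as fixed effects and participants are included as random effects". It lists no group-by-time term and names no residual covariance or standard-error method. The hypothesis in the Objectives section likewise refers to both visits.

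Only one measure of spread is given: "the estimated standard deviation of change in muscle strength (measured through leg press) from baseline to pretransplant is 16.8 kg". From it the section concludes that "this study will detect a between-group mean difference of 19.3 kg with 80% power". No SD is given for the posttransplant change, and no correlation between the visits.

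**The concern.** A participant random effect with an ordinary residual is a random-intercept model. With two post-baseline visits it implies compound symmetry: both visits have the same total variance. Conditioning treatment, admission and recovery lie between the two visits, and patients may recover unevenly, so the spread of change could differ between them. The article offers nothing to support equality.

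Once a group difference is read at one visit, its standard error under this model rests on the average of the two visit variances. It is too large at the less variable visit and too small at the more variable one. If the posttransplant change is the more variable, the pretransplant comparison loses power and the posttransplant comparison rejects too often. If it is the less variable, the errors reverse. Adding a group-by-time term alone would not help, because the visit-specific contrasts are where the shared variance acts.

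**Working it through.** **Inputs from the article.** Two-sided alpha 0.05 ("at .05 two-sided α level"), 15 randomised per group, "taking account of 10% dropout", d = 1.15, SD 16.8 kg for the pretransplant change, detectable difference 19.3 kg.

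**Assumptions, because the article gives no figure.** Ratio k of posttransplant to pretransplant SD from 0.75 to 1.5; between-visit correlation 0.5 to 0.7; complete data; 13 analysed per arm; no true effect at follow-up.

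**Step 1: the plan's own figure.** 19.3 / 16.8 = 1.149, which is the stated d. Allowing for dropout, 15 x 0.9 = 13.5 per arm. A two-sample t-test (noncentral t) with 13 per arm has 80.3% power for d = 1.15, and 80% power corresponds to d = 1.145, or 19.24 kg. The stated figures are reproduced. They come from a single-visit calculation that does not use the mixed model.

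**Step 2: standard errors at each visit.** Let s1 and s2 be the SDs of change at the two visits, with k = s2/s1. With n per arm, the true variance of the group difference at visit t is 2 x st^2 / n. A balanced random-intercept model with group-by-time uses 2 x [(s1^2 + s2^2)/2] / n at both visits. The ratios of model SE to true SE are therefore:

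- pretransplant: sqrt((1 + k^2)/2)
- posttransplant: sqrt((1 + k^2)/2) / k

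For k = 1.5 these are sqrt((1 + 2.25)/2) = sqrt(1.625) = 1.275, and 1.275/1.5 = 0.850. For scale, the true pretransplant SE is 16.8 x sqrt(2/13) = 6.59 kg; the shared-variance model would report on average about 6.59 x 1.275 = 8.40 kg.

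**Step 3: simulation.** 40,000 trials per setting, random intercept plus group-by-time, Satterthwaite degrees of freedom:

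| SD ratio post/pre | SE ratio, pre | SE ratio, post | Pretransplant power, d = 1.15 | Posttransplant type I error |
|---|---|---|---|---|
| 0.75 | 0.884 | 1.179 | not comparable (SE 12% too small; type I error there about 8%) | about 2% |
| 1 | 1.000 | 1.000 | 81% | 5% |
| 1.25 | 1.132 | 0.906 | 73-74% | 7-8% |
| 1.5 | 1.275 | 0.850 | 63-64% | about 9.5% |

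The between-visit correlation hardly matters. With a separate variance for each visit, pretransplant power stays at about 80% and posttransplant type I error at about 5% in every row.

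**Step 4: the averaged effect.** The listed fixed effects, without an interaction, estimate one group difference averaged over the two visits. With complete data its 95% interval kept 94.8% to 95.3% coverage at every ratio tried, including a ratio of 2. Its inference is not distorted.

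**The case against.** A reader might infer that the plan commits to equal variances and that its visit-level error bars are wrong. The documents do not support that, for four reasons.

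- The article never says that the participant effect is the only covariance component or that residual variance is equal at the two visits. A participant effect can be combined with visit-specific residual variances or robust standard errors. An article may also leave covariance detail to a full protocol or analysis plan that is not shown here.
- Unequal spread is plausible but not shown. A ratio of 2 would give 41% power and 12% type I error, but the article has no figure that points to such a ratio. At ratio 1 nothing is lost.
- The listed terms contain no interaction. Taken literally, they yield only the averaged effect, whose interval is sound.
- The 80% power statement is a single-visit t-test calculation in kilograms, whereas the primary analysis is of adjusted percent change. The link between the power loss computed here and the stated power is therefore loose.

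All of this stands, and it limits the point to a conditional one. It does not remove it. The article did name a within-participant structure, and a statistician following that sentence would ordinarily fit a random intercept. The article also states that the model is to compare the groups at both visits. Meeting that aim requires visit-specific contrasts, and for these the named structure is valid only if the spread is equal.

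**Conclusion.** The point holds as a conditional weakness in the named method, not as a demonstrated error. It rests on three things: the ordinary reading of the participant random effect (random intercept, common residual variance), visit-specific group differences being reported, and the spread of change differing between visits. The first two follow naturally from the article's text; the third is an assumption. Over SD ratios of 0.75 to 1.5, the consequences run from a slightly conservative to a moderately liberal posttransplant test, with a pretransplant power loss of roughly 7 to 17 points when the posttransplant spread is larger (80 - 73 and 80 - 63). No figure stated in the article changes. For a pilot-sized trial this is a worthwhile, low-cost improvement and no more than that.

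**What to change.** Estimate the visit-specific group differences from a repeated-measures model with an unstructured 2x2 covariance over the two post-baseline visits and small-sample degrees of freedom, in place of the participant random intercept. The model needs a group-by-time term so that each visit's difference can be read from it. Letting the baseline coefficient differ by visit is optional and separate from this point.

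The cost is a sentence of analysis wording, one extra variance parameter, and about 1 point of power if the two variances turn out equal (81% against 80%). No new data are needed. If a fuller analysis plan already allows the variance to differ by visit, saying so closes the point.
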